| Throughout                                                                                                                  | Updated total number of dyads FROM 66 TO 86. This means the total participant population is being increased FROM 132 TO 172.                                                                                                                                                                                                                                                                                                                                                                         | The number of dyads who were above the 75 th percentile for the 1 st set of LENA recordings has been higher than expected. This means there would not be enough dyads entering the phase 2 part of the study to do a proper statistical analysis. The goal is to have at least 66 dyads entering into the second phase of the study (i.e., to be eligible for the 2 nd LENA recording). |
| Throughout                                                                                                                  | Changed TWMB intervention (i.e., ages for which the intervention was given at the WCC visits) FROM children who are "< 36 months" of age TO children who are "4 to 36 months of age"                                                                                                                                                                                                                                                                                                                 | To increase recruitment windows by keeping children ages 0 to 3 months(+30) days naïve to the TWMB intervention.                                                                                                                                                                                                                                                                                                         |

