Complete LENA data will be defined as follows: at least one usable recording (i.e., usable recording from one day of the two possible recording days) is collected from caregiver participants within two attempts (to account for potential errors in recording) at Post-Intervention.

We will monitor completeness/usability of LENA throughout baseline data collection to optimize our strategies for collecting follow-up data. Many studies using LENA have obtained 100% usable data at baseline, with other studies reporting a range of 70–100% usable data. In our own lab, we have obtained 93% usable LENA data with underserved and low-SES populations. Usable data includes compliance with wearing the LENA vest and adequate length of recording time. We will ensure caregiver understanding of LENA recording procedures by sending a LENA “how-to” video and written/visual instructions to caregivers and by completing a follow-up phone call to walk caregivers through using LENA, check for caregiver understanding of instructions, and answer any questions (see detailed procedures in the study-specific MOP). We will track reasons for unusable data.

If data usability obtained in TWMB at Baseline drops below 70%, we will conduct a root-cause analysis and present a plan for correcting the problem to the DSMB. If the source of unusable data could not be corrected, we will re-evaluate our plan to collect LENA at Post-intervention.

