### 9.2 SAMPLE SIZE DETERMINATION

The primary endpoint is a binary variable of reaching at least a 10% increase in AWC or CTC percentile scores from Baseline (Week 1) to Post-intervention (Week 48). This increase is based on previous language-promotion intervention studies using LENA, which reported statistically significant gains (for intervention versus control) for parent language-promotion behaviors ranging from 10-30%. In terms of clinical relevance, the proposed 10% gain in AWC would be an increase of ~160 adult words per hour, which equates to an increase of ~3 points in child language standard scores on the Bayley Scales of Infant Development and the Preschool Language Scale (proposed two-point increase for every increase of 100 adult words per hour for children age birth to four years-old).

The study is expected to have at least 70% of caregiver participants reaching improvement in language-promotion behaviors at the end of the study. In other words, the targeted rate of improvement in language-promotion behaviors is 70%. We plan a total accrual of up to 86 child-caregiver dyad participants into the study with a goal of having at least 66 dyads enter into phase II of the study. With an estimated phase II attrition rate of 20%, we expect that a total of 53 enrolled child-caregiver dyad participants will complete phase II of the study and hence the effective sample size is 53. Using a two-sided exact test with a significance level of 0.05, we are able to reach 85% power to reject a null rate of improvement at 50%, should the targeted rate of improvement be reached.

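### Section 9.2 claims 85% power, but the exact test it names gives 78.4% at the stated n of 53, and the path from 86 consented dyads to 53 has no stated allowance for unusable baseline recordings

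*Protocol*

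**What the plan says.** Protocol section 9.2 sets the size in three steps.

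- **Consent to Phase II.** The design is for "a total accrual of up to 86 child-caregiver dyad participants into the study with a goal of having at least 66 dyads" in Phase II. Entry requires a baseline LENA score at or below the 75th percentile of the age norms (sections 5.1.2 and 5.5.2.1).
- **Phase II to analysis.** "With an estimated phase II attrition rate of 20" per cent, the section counts on 53 dyads finishing Phase II and concludes: "hence the effective sample size is 53".
- **Power.** "Using a two-sided exact test with a significance level of 0.05", a true improvement rate of 70% is said to give 85% power against a null rate of 50%.

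Section 8.1.2 gives the recording yield. Some studies obtained 100% usable data at baseline and others ranged from 70% to 100%. For the team itself: "In our own lab, we have obtained 93% usable LENA data with underserved and low-SES populations". Each assessment has two recording days, and an unusable recording leads to a second attempt. Section 7.2 counts Phase 1 participants who do not proceed as early-terminated and says that early-terminated caregivers are not replaced.

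The version 08 change summary explains the rise from 66 to 86 dyads: the number above the 75th percentile on the first "set of LENA recordings has been higher than expected". It gives neither the expected nor the observed share.

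**The concern.** There are two separate questions. The first is whether the named test gives 85% power at n = 53. The second is whether 86 consented dyads can be expected to yield 53 analysed. The step from 86 to 66 has no stated pass rate and no factor for recordings that cannot be scored, although section 8.1.2 treats usability as a real source of loss.

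If either step fails, the protocol overstates the trial's chance of rejecting 50% when the true rate is 70%. A non-significant result would then be read against a power that the design does not have, and the planning of the later randomised trial would start from that reading.

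**Working it through.** **Inputs.** From section 9.2: up to 86 consented, 66 in Phase II, 20% attrition, n = 53, null 0.50, target 0.70, two-sided exact test at 0.05, stated power 85%. From section 8.1.2: usability of 93% (own laboratory) and 70–100% (other studies). Assumed, because the protocol gives no figure: 75% of dyads pass the cut, as a norm-like sample would on one score; usability acts per dyad; losses are independent.

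**1. Effective n.** 66 × (1 − 0.20) = 52.8, rounded to 53. This reproduces.

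**2. Power at n = 53.** The rule is the smallest r with 2 × P(X ≥ r | 53, 0.50) ≤ 0.05.

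| r | two-sided p under 0.50 | P(X ≥ r) under 0.70 |
|---|---|---|
| 34 | 0.0534 | 85.9% |
| 35 | 0.0270 | 78.4% |

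A count of 34 does not meet 0.05, so the critical count is 35 and power is 78.4%. The stated 85% does not reproduce. The normal approximation gives Φ[(0.20 − 1.96 × √(0.25/53)) / √(0.21/53)] = 85.05%, which is the likely source.

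**3. Exact power at nearby n.** It rises and falls as the critical count steps up.

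| n | 37 | 39 | 42 | 44 | 45 | 46 | 47 | 48 | 49 | 51 | 52 | 53 |
|---|---|---|---|---|---|---|---|---|---|---|---|---|
| power, % | 69.8 | 61.8 | 74.3 | 77.8 | 74.6 | 71.3 | 78.0 | 74.9 | 81.0 | 83.6 | 81.1 | 78.4 |

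No n from 34 to 53 reaches 85%; the maximum is 83.6% at n = 51. Over 37 to 49 the range is 61.8% to 81.0%.

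**4. From 86 to Phase II.** 66/86 = 76.7%, so losses from the cut and from unusable or unreturned recordings must together stay within 20 dyads.

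- Cut alone at 75%: 86 × 0.75 = 64.5, which is 1.5 short of 66. The chance of at least 66 of 86 is 41%.
- Cut and 93% usable: 86 × 0.75 × 0.93 = 60.0. The chance of at least 66 is 10%.
- Pass rate needed for 66 with 93% usable: 66/(86 × 0.93) = 82.5%.
- At 70% usable: 86 × 0.70 = 60.2 dyads have a score, so 66 cannot be reached at any pass rate.

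**5. From Phase II to analysis.**

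- If the 20% already includes unusable follow-up recordings: 60.0 × 0.80 = 48.0, exact power 74.9%.
- If it does not: 48.0 × 0.93 = 44.6, exact power 77.8% at n = 44 and 74.6% at n = 45.
- With 66 in Phase II and usability applied at follow-up only: 66 × 0.80 × 0.93 = 49.1 (81.0% at n = 49), or with 0.70, 37.0 (69.8% at n = 37).

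**6. How much comes from where.** At n = 53, moving from 85% to the exact test costs 6.6 points. On the normal approximation, going from 53 to 45 lowers power from 85.1% to 78.5%, and from 53 to 48 lowers it to 81.2%. On the exact scale, going from 53 (78.4%) to 45 (74.6%) costs about 4 points.

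**The case against.** The strongest reply concerns the 86–66–53 chain.

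- **Ceiling and goal.** The 86 is a maximum and the 66 a target, so a possible shortfall is an unsupported assumption and not an arithmetic slip. This stands.
- **Unknown pass rate.** The trial recruits at-risk families and contacts Medicaid or uninsured families first, so more than 75% might pass. At 80%, with all baselines usable, the chance of at least 66 is 81%. The rate also depends on whether adult word count, conversational turns or both must be at or below the cut, which the protocol does not settle. At norm level, with a correlation of 0.5 to 0.9 assumed between the two scores, about 62–69% pass if both must and 81–88% if either suffices. This stands.
- **Usability.** The 93% and 70–100% figures are not said to be per dyad. One usable day out of two is enough for complete post-intervention data, and there is a second attempt, so the loss per dyad may be smaller. The 20% may already cover missing follow-up recordings, since section 7.3 ties loss to follow-up to the recording. This stands.
- **Pilot purpose.** Section 9.4.2 makes an exact confidence interval the main summary and the test an alternative. That lowers the stakes but leaves the stated power wrong.

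A reader might infer from the version 08 rationale that 86 is too few. The text does not support that. It explains why the number was raised, and 86 may have been set from the observed rate. A reader might also infer that the analysed sample will certainly fall well below 53, or that lost dyads explain most of the gap from 85%. The first needs a pass rate that is not in the protocol. The second is wrong under the central assumptions, because the larger part comes from the exact test at n = 53.

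None of this answers the power calculation in step 2 of the working, which uses only section 9.2's own inputs.

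**Conclusion.** The point holds in two parts of different strength.

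**Firm:** power at the stated n = 53 is 78.4%, not 85%, for the test that section 9.2 names. This needs no assumption beyond that section's inputs and the usual rule of doubling the one-sided tail.

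**Conditional:** the chain to 53 has no stated margin for unusable baseline recordings. With a 75% pass rate and 93% usability per dyad, about 60 dyads would enter Phase II and 45 to 48 would be analysed. Exact power is then about 75% at either end of that range, and 71% to 78% across it. A higher pass rate or a successful resend would narrow or close the shortfall. A requirement that both scores pass would widen it.

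Because exact power is not monotone, a smaller n does not always mean lower power: 49 analysed has more (81.0%) than 53. The supported conclusion is that 85% is not delivered at 53 or at any n from 34 up to it.

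**What to change.** In section 9.2:

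1. Replace 85% with the exact power, 78.4% at n = 53, and state the critical count of 35.
2. Restate the expected Phase II entry and the effective n from the qualifying and usability rates already observed at baseline. The 60 and 45–48 above are illustrations and should not be copied in.
3. Say which score or scores the 75th-percentile cut applies to, and whether the 20% attrition includes unusable follow-up recordings.
4. Give exact power over the plausible range of n, noting that it is not monotone. For 37 to 49 analysed it runs from about 62% to 81%.

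This is a wording change that uses screening data the sponsor should already hold. No dyads need be added. The cost is a less favourable stated power.

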#### 9.4.2 ANALYSIS OF THE PRIMARY EFFICACY ENDPOINT

The primary endpoint of improvement in caregiver language-promotion behaviors (as measured by LENA) will be summarized using frequency (in %). A 95% confidence interval will be constructed using a Clopper-Pearson exact method. Alternatively, a hypothesized null rate can be tested using a two-sided exact test at a significant level of 0.05.

---

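### Section 9.2 states 85% power for a two-sided exact test with 53 completers; the conventional exact test has 78.4%.

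*Protocol*

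**What the plan says.** Section 9.2 gives every input to the power calculation. The endpoint is binary. The target is stated as "the targeted rate of improvement in language-promotion behaviors is 70" per cent. Up to 86 dyads are to be enrolled, "with a goal of having at least 66 dyads enter into phase II of the study". Attrition enters as "With an estimated phase II attrition rate of 20" per cent, "hence the effective sample size is 53". The conclusion reads: "Using a two-sided exact test with a significance level of 0.05, we are able to reach 85% power". The null rate to be rejected is 50%, and the power is claimed for a true rate equal to the 70% target.

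Section 9.4.2 plans the matching analysis: "A 95% confidence interval will be constructed using a Clopper-Pearson exact method". As an alternative, "a hypothesized null rate can be tested using a two-sided exact test at a significant level of 0.05". Neither section mentions an approximate test or a mid-p adjustment.

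**The concern.** A one-sample exact binomial test can use only whole-number cutoffs, so its true size is usually below the nominal 0.05 and its power is below what a smooth large-sample formula predicts. A power of 85% with 53 observations, 50% against 70%, is close to the textbook large-sample value, which raised the question of whether it holds for the exact test.

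This is the only power statement in the protocol. The summary of changes for version 08 gives the aim of at least 66 dyads in the second phase as the reason for raising enrolment from 66 to 86 dyads. The step from 66 to 53 to a stated power is therefore the published justification for the trial's size. If the power is wrong, the chance of missing a true 70% rate is understated. Nor would a reader learn that 34 of 53 improvers (64%) is not enough to reject 50%.

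**Working it through.** **Inputs (protocol section 9.2).** Null rate p0 = 0.50; target p1 = 0.70; two-sided alpha = 0.05; 66 dyads in phase II; 20% attrition.

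**Step 1: effective sample size.** 66 × 0.80 = 52.8, rounded to 53. The plan's figure reproduces.

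**Step 2: rejection region of the exact test.** Under Binomial(53, 0.5):

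| Improvers | Upper tail | Two-sided p | Clopper-Pearson lower limit | Rejects 50%? |
|---|---|---|---|---|
| 34 | 0.0267 | 0.0534 | 0.498 | no |
| 35 | 0.0135 | 0.0270 | 0.517 | yes |

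The upper cutoff is 35 of 53 (66.0%), and by symmetry the lower cutoff is 18. The actual size is 2 × 0.0135 = 0.0270. At p0 = 0.5 the null distribution is symmetric, so the usual non-randomised two-sided exact tests share this region, and the Clopper-Pearson interval leads to the same decision.

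**Step 3: power.** Under Binomial(53, 0.7), P(X ≥ 35) = 0.7844; P(X ≤ 18) is negligible. Power is 78.4% and the type II error is 21.6%. The shortfall is 85 − 78.4 = 6.6 points.

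**Step 4: what does give about 85% at n = 53?**

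- Normal approximation, no continuity correction: Φ[(0.20·√53 − 1.96·0.5)/√0.21] = Φ[(1.456 − 0.980)/0.4583] = Φ(1.039) = 85.05%.
- Arcsine: Φ[2(arcsin√0.7 − arcsin√0.5)·√53 − 1.96] = 84.99%.
- Uncorrected score test or mid-p test, either of which rejects at 34: P(X ≥ 34 | 0.7) = 85.9%, with actual size 0.0534.
- Randomised exact test of size exactly 0.05: it rejects at 34 with probability (0.025 − 0.0135)/(0.0267 − 0.0135) ≈ 0.870. Since P(X = 34 | 0.7) = 0.8592 − 0.7844 = 0.0748, power is 0.7844 + 0.870 × 0.0748 ≈ 84.95%.

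With a continuity correction the normal formula gives 81.3%.

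**Step 5: sensitivity to the number of completers.** Conventional exact test, p1 = 0.70:

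| Completers | Cutoff | Actual size | Power |
|---|---|---|---|
| 51 | 33 | 0.049 | 83.6% |
| 52 | 34 | 0.036 | 81.1% |
| 53 | 35 | 0.027 | 78.4% |
| 54 | 35 | 0.040 | 83.7% |
| 55 | 36 | 0.030 | 81.3% |
| 56 | 36 | 0.044 | 85.9% |
| 57 | 37 | 0.033 | 83.7% |
| 58 | 37 | 0.048 | 87.9% |
| 59 | 38 | 0.036 | 85.9% |
| 60 | 39 | 0.027 | 83.8% |
| 61 | 39 | 0.040 | 87.9% |

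Power first reaches 85% at 56, dips below it at 57 and 60, and stays above it from 61.

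**Step 6: what 85% would require.** At 20% attrition, 56 completers need 56/0.8 = 70 phase II dyads, and 61 need 61/0.8 = 76.25, so 77. With 66 dyads held fixed, 56 completers mean attrition of 1 − 56/66 = 15.2%, and 61 mean 1 − 61/66 = 7.6%.

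**The case against.** The best defence is that 53 is a projection. Phase II entry is a goal of at least 66 and attrition is an estimate, so the final count may differ, and 53 is a local low point: one more completer brings exact power to 83.7%, only 1.3 points short. This stands as a limit on the size of the error, and the range over 51 to 55 should be reported. It does not rescue the statement, because section 9.2 attaches its 85% to 53, and no count from 51 to 55 reaches 85%.

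A second defence is that this is an uncontrolled pilot, that section 9.4.2 puts the estimate and interval first, and that the test is an alternative. That is fair: the misstatement changes no estimate, no interval and no type I error, and the exact test remains valid and conservative. But the interval leads to the same decision at 34 and 35, and section 9.2 ties its figure to the exact test. A pilot may run at 78% power; it should not report 85%.

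A reader might infer that the 85% was certainly computed with a normal approximation and mislabelled. The protocol does not say how it was computed. The near match makes this plausible, but the arcsine formula and a randomised exact test fit as well. The same example shows that not every test that could be called exact has the same power. The randomised test reaches about 85%, but nothing in the protocol suggests it, and the Clopper-Pearson interval points to the conventional test.

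**Conclusion.** The stated power is wrong for the analysis that the protocol names. With 53 completers, a 50% null and a true rate of 70%, the conventional two-sided exact test at 0.05 has 78.4% power against the stated 85%, and an actual size of 0.027. The result rests only on the inputs of section 9.2 and on reading the exact test as the usual non-randomised binomial test, which the Clopper-Pearson interval of section 9.4.2 supports.

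Two limits apply. The 6.6-point gap is specific to exactly 53 completers; over 51 to 55 the shortfall runs from 1.3 to 6.6 points. And the origin of the 85% is not documented, so the finding concerns the figure and not how it arose.

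One might also conclude that 56 completers would secure 85%. They would not: 57 and 60 fall back to 83.7% and 83.8%.

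**What to change.** In section 9.2, replace the power sentence with one stating that 53 completers give about 78% power under the two-sided exact test at 0.05 (null 50%, true rate 70%), and that power ranges from 78% to 84% for 51 to 55 completers. The cutoff of 35 of 53 may be added as an illustration, marked as to be recomputed for the number actually observed.

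If the sponsor prefers to keep 85%, section 9.2 should say that exact power first reaches it at 56 completers and stays above it only from 61. It should add that 66 phase II dyads with 20% attrition do not deliver this, and adjust the phase II goal or the attrition assumption to match (step 6 of the working gives the numbers).

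The first option costs one sentence and a less favourable figure. It needs no change to enrolment, endpoint or analysis.

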### 9.3 POPULATIONS FOR ANALYSES

The population of interest is the child-caregiver dyads participating in the study.

### 9.4 STATISTICAL ANALYSES

#### 9.4.1 GENERAL APPROACH

Following finalization of the protocol but prior to data lock, the DCOC statistical team will issue a Statistical Analysis Plan (SAP) as a separate document, which will provide detailed analytical plans for the set of analyses outlined below. The statistical team will conduct all statistical analyses following the statistical principles for

clinical trials as specified in ICH Statistical Principles for Clinical Trials (ICH Topic E9). The study team will describe and justify any deviations from the planned analyses in the final integrated clinical study report. The study team will present all study data and summary tables for the overall study and by study sites.

**Descriptive Statistics:** All numerical variables will be summarized using mean  $\pm$  standard deviation and median (minimum, maximum). All categorical variables will be summarized using frequency (in %). Numerical variables will also be inspected of outliers and empirical distributions during data review. Methods for handling outliers and skewed data will be defined and described in the SAP.

Descriptive statistics of the primary endpoints will be reported by caregiver-child demographics (such as race), Medicaid status (yes/no) and WCC visit age (e.g., 2, 4, 6, 9, 15, 18-month WCC visit). The statistics summarized will be used to inform the future RCT.

---

#### 9.4.2 ANALYSIS OF THE PRIMARY EFFICACY ENDPOINT

The primary endpoint of improvement in caregiver language-promotion behaviors (as measured by LENA) will be summarized using frequency (in %). A 95% confidence interval will be constructed using a Clopper-Pearson exact method. Alternatively, a hypothesized null rate can be tested using a two-sided exact test at a significant level of 0.05.

---

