The study team will enroll a sample of child-caregiver dyads in each clinic whose child members are between age zero and nine months (+0 to 30 days) old. We include this age range for the child participants (rather than children between 4 and 36 months of age) to minimize variability due to development within the sample. The study team will enroll child-caregiver dyads where the child is a patient of a participating provider at each clinic. Additionally, the existing initiative for patient-centered medical homes (empanelment of patients to specific providers or care teams) will help to ensure that participating children will continue to follow up with the same trained TWMB primary providers for the majority of their WCC visits. Existing primary care empanelment will help to decrease some of the provider-to-provider variability in delivering TWMB by ensuring that that child is following up with the same provider as frequently as possible during the study period. In clinics where the patient-centered medical home is not fully operational, study staff will work closely with clinic staff to maximize follow up in subsequent WCC visits with the same provider to ensure continuity. In addition, the benefits of patient empanelment will be underscored during provider and care team TWMB training sessions.

*To ensure dyads are naïve to the TWMB intervention, we will enroll the majority of our sample of dyads prior to completing TWMB training for clinic providers; after training has been completed, we will only enroll dyads who are TWMB naïve due to age and/or not having a previous WCC visit with TWMB. This approach is common in behavioral intervention trials and important in situations where the intervention training may change the*

*standard-of-care practices (i.e., in this case, it could change the anticipatory guidance providers give to families related to language milestones and language development prior to enrolled dyads completing their baseline LENA assessment).*

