Note that in the future RCT, we will randomize participants at the clinic level to the TWMB intervention or care as usual control to evaluate TWMB efficacy for caregiver language-promotion behaviors, as well as child language outcomes. The large-scale efficacy trial will be adequately powered to include the continuum of home language environments and will not employ LENA cutoffs for enrollment. In the large-scale trial, it will also be possible to follow children over a longer period to allow evaluation of language outcomes across a wider age range.

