## 5 STUDY POPULATION

TWMB will take place in 2 clinics in ECHO ISPCN states. Clinic criteria are broadly inclusive to increase the likelihood of success of a future RCT and enhance the generalizability of results. Within each clinic, we will have up to 4 providers or provider/care team members in this pilot study (for a maximum of 8 providers). Note that “provider” is used herein to refer to health providers and care team members (e.g., including physicians, physician assistants, nurse practitioners, nurses, and nursing assistants). In the case of a single-provider rural clinic, we will include the provider and at least 1 member of their care team. See Inclusion Criteria for Clinics, Section 5.1.1.

Within each clinic, we will recruit and enroll child-caregiver dyads whose child has an upcoming WCC appointment with a participating provider. We will recruit children aged zero to nine months (+ 0-30 days) between 0-30 days before their WCC visit, which will occur per provider’s clinical discretion and routine AAP periodicity schedule and follow them up to four consecutive WCC visits during the 12 months of intervention or 13 months total - whichever comes first. This will maximize recruitment potential and capture a range of caregiver language behaviors with children of varying ages within the time constraints of the pilot study. We will recruit dyads with a child who receives primary care from a participating provider in this pilot study. Within each clinic, we will aim for an equal allocation ratio regarding age at recruitment. Furthermore, we will prioritize including families with lower SES by first contacting for participation those families whose children have Medicaid insurance.

This approach will also be employed in the future full-scale RCT, which will add randomization at the clinic level to either TWMB intervention or care as usual control.

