#### 9.4.8 EXPLORATORY ANALYSES

We will examine barriers to enrollment, including our ability to contact caregivers, the proportion of caregivers that consent to participate in the study, enrollment of caregiver-child dyads, and caregivers' willingness to

complete baseline assessments. We will also examine characteristics related to attrition for caregiver and provider participants. Descriptive statistics will be used in these exploratory analyses.

Caregiver language promotion behaviors (LENA) will be examined and reported descriptively. Child vocalization scores (LENA) will be reported descriptively. We will also examine associations of differences in change in LENA scores with caregiver characteristics (e.g., low, or high baseline LENA scores, education level, SES) using analysis of variance (ANOVA) models or linear regression models.

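### The primary interval and test treat 53 dyads from at most 8 providers in 2 clinics as independent, so coverage and type I error are not protected if the result is generalised beyond them

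*Protocol*

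**What the plan says.** Section 9.4.2 of the Protocol summarises the primary endpoint as a frequency and then fixes the method: "A 95% confidence interval will be constructed using a Clopper-Pearson exact method". A two-sided exact test of a null rate at the 0.05 level is offered as an alternative.

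Section 9.2 takes 66 dyads entering phase II, applies 20% attrition, and says the investigators "expect that a total of 53 enrolled child-caregiver dyad participants will complete phase II of the study and hence the effective sample size is 53". The power statement that follows names an exact two-sided test at the 0.05 level and, for a true rate of 70%, claims: "we are able to reach 85% power to reject a null rate of improvement at 50" (per cent).

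On where the dyads come from, section 5 says that in each clinic "we will have up to 4 providers or provider/care team members in this pilot study (for a maximum of 8 providers"). The synopsis gives the range as 1 to 4 selected providers at each of the 2 clinics. On delivery, section 4.2.1 says "Existing primary care empanelment will help to decrease some of the provider-to-provider variability in delivering TWMB", so it expects some of that variability to remain. The same section says that "in the future RCT, we will randomize participants at the clinic level".

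The only mention of site in the planned analyses is that data, tables and safety summaries are shown overall and by site (9.4.1 and 9.4.3). Sections 9.2 to 9.4.2 contain no ICC, design effect, stratification or cluster-robust method.

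**The concern.** A Clopper-Pearson interval and a one-sample exact test both model the number of improvers as binomial with 53 independent trials. Dyads who share a provider share that provider's coaching, and dyads who share a clinic share its workflow and case mix. If this makes outcomes positively correlated, the pooled proportion varies more across new sets of providers or clinics than the binomial formula allows.

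That matters because the pilot looks beyond its own sample. Sections 4.2.1 and 5 invoke generalisability. Section 4.2.1 also justifies omitting a control group partly by the wish to estimate variability in response for a trial randomised by clinic, and an interval that assumes independence can understate that variability. By-site tables do not alter the pooled interval or the test.

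This is more than detail left to the SAP. The interval, the test, the significance level and the sample size behind the power statement are all fixed in the protocol.

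**Working it through.** **Inputs from the Protocol.** n = 53 (66 × 0.8 = 52.8), null rate 50%, target rate 70%, two-sided alpha 0.05 (9.2); 2 clinics and at most 8 providers (5).

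**Assumptions.** The ICC is not given, so 0.01, 0.05 and 0.10 are used. Cluster sizes are taken as near equal: 8 providers (five of 7, three of 6), 4 providers (14, 13, 13, 13) or 2 clusters (27, 26). The 2-cluster case stands for correlation at clinic level or for one provider per clinic.

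**Step 1: the plan's own figure.** At n = 53 the exact test rejects at 35 or more, or 18 or fewer. Its size is 2 × P(X ≥ 35 | 0.5) = 2.7%, and its power is P(X ≥ 35 | 0.7) = 78.4%, not 85%. Rejecting from 34 upward would give 85.9% power but a two-sided size of 5.3%. The stated 85% matches a normal approximation: Φ((0.2√53 − 1.96 × 0.5)/√0.21) = 85.1%. Under independence, Clopper-Pearson coverage at 70% is 96.3%.

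**Step 2: design effect.** DE = 1 + (Σm²/n − 1) × ICC, where m is the cluster size, and effective n = n/DE. At ICC 0.05:
- 8 providers: Σm² = 353; DE = 1 + (6.660 − 1) × 0.05 = 1.283; effective n = 41.3.
- 4 providers: Σm² = 703; DE = 1 + (13.264 − 1) × 0.05 = 1.613; effective n = 32.9.
- 2 clusters: Σm² = 1405; DE = 1 + (26.509 − 1) × 0.05 = 2.275; effective n = 23.3.

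**Step 3: behaviour of the planned interval and test.** The total was given its exact distribution as a sum of independent beta-binomial clusters. Size is at 50%; power and coverage are at 70%.

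| Clusters | ICC | Effective n | Size | Power | Coverage |
|---|---|---|---|---|---|
| 8 | 0.01 | 50.2 | 3.2% | 77.8% | 95.8% |
| 8 | 0.05 | 41.3 | 5.1% | 75.8% | 93.5% |
| 8 | 0.10 | 33.8 | 7.8% | 73.9% | 90.4% |
| 4 | 0.01 | 47.2 | 3.7% | 77.2% | 95.1% |
| 4 | 0.05 | 32.9 | 8.3% | 73.6% | 89.9% |
| 4 | 0.10 | 23.8 | 14.2% | 70.8% | 83.5% |
| 2 | 0.01 | 42.2 | 4.9% | 76.0% | 93.8% |
| 2 | 0.05 | 23.3 | 14.7% | 70.6% | 83.0% |
| 2 | 0.10 | 14.9 | 25.3% | 67.5% | 72.0% |

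**Step 4: break-even ICCs.** Size passes 5% above an ICC of about 0.048 (8 providers), 0.022 (4) or 0.011 (2 clusters). Coverage at 70% falls below 95% above about 0.024, 0.011 and 0.005. Unequal loads make this worse: provider sizes 20, 12, 8, 4, 4, 2, 2, 1 give a size of 7.8% at ICC 0.05.

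**Step 5: can it change the conclusion?** At 35 of 53, the smallest count that rejects upward, the planned interval is 51.7% to 78.5%. At the effective n for ICC 0.05 it is 49.7% to 80.0% (8 providers) or 47.5% to 81.6% (4 providers), and 50% is no longer excluded.

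**The case against.** A reader might infer that the interval is too narrow and that the false-positive rate exceeds 5%. The documents do not support either as a statement of fact. Both depend on an ICC that is not given, and the discreteness of the exact test leaves room: size starts at 2.7%, and with 8 equal providers 5% is passed only above an ICC of about 0.048.

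If these clinics and providers are taken as fixed, the interval is not too narrow at all. With provider-specific rates pᵢ, the variance of the total is Σmᵢpᵢ(1 − pᵢ), which is at most the binomial np(1 − p) at the average rate p. Section 9.3 supports that reading, since it defines the population of interest as the participating dyads. This objection stands, and it is why the point concerns generalisation.

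The effective sample size in 9.2 follows directly from attrition, so it means evaluable dyads. It should not be read as a claim that clustering was considered and ruled out.

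Variable delivery cannot correlate outcomes if the intervention has no effect, so type I inflation needs shared case mix or clinic circumstances, for which the documents give no evidence. That weakens the type I argument but not the coverage argument at 70%. Nesting is also imperfect: under 6.1.2 another trained provider in the practice may see a dyad. That dilutes provider correlation and moves some of it to the clinic, where the figures are worse.

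The test is optional and the aim is exploratory, so the stakes are moderate.

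Two further inferences should be resisted. One is that the exploratory models omit clinic: 9.4.8 only names the model families, "using analysis of variance (ANOVA) models or linear regression models", and covariate lists belong to the SAP. The other is that the primary interval should be replaced by one at a single assumed ICC, which would make the main result rest on a number that the documents do not supply.

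**Conclusion.** The point holds in conditional form. The nesting is in the protocol, and the primary interval and test ignore it. For a claim limited to these two clinics and their participating providers, the Clopper-Pearson interval is adequate. For any wider claim, its coverage and the test's type I error are not protected.

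How much this matters depends on how many providers contribute and at what level the correlation sits. It is small with 8 equal providers at an ICC near 0.01, appreciable with 4 providers at 0.05, and severe if the correlation is at clinic level. These figures rest on the assumed ICC range, near-equal cluster sizes and a beta-binomial model. Two clinics cannot support a usable estimate of clinic-level variance, so the analysis cannot settle the matter from its own data.

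Separately, the 85% power in 9.2 does not belong to the exact test named there, whose power is 78.4% even under independence.

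**What to change.** 1. **Section 9.2.** Describe 53 as the expected number of evaluable dyads, not the effective sample size. State effective n and power for the planned test over an ICC range. With 8 equal providers and ICC 0.01 to 0.10, effective n is about 50 to 34 and power about 78% to 74%. Correct the 85% to 78.4% under independence.

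2. **Section 9.4.2.** Keep the Clopper-Pearson interval as primary and say that it applies to these two clinics and their participating providers. Report the rate with an exact interval for each clinic. Add a prespecified sensitivity interval and test at n/DE, with DE = 1 + (sum of squared provider sizes/n − 1) × ICC, for ICC 0.01, 0.05 and 0.10. Assign each dyad to its enrolling participating provider, which settles the case of a dyad seen by several providers. If the conclusion changes over that range, make no efficacy claim beyond these clinics.

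**Cost.** Wording in two sections and a few lines of code. No new data are needed, because the clinic is known and 8.1.2 already logs the provider at each visit. The downside is a wider sensitivity interval and a less favourable stated power. For 37 of 53, the interval goes from 55.7%–81.7% to 53.6%–83.1% (8 providers) or 51.4%–84.5% (4 providers) at ICC 0.05. The sensitivity test is also slightly conservative. If the true ICC is 0.05, it has size 2.8% and power 67.2% with 8 providers, or 2.9% and 56.9% with 4. That is acceptable for a supporting analysis and is a further reason not to make it primary.
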